## Abstract

**Background:**

Potentially inappropriate prescribing is common among older adults with multimorbidity due to various reasons, from concurrent application of multiple single-disease clinical guidelines to fragmentation of care. Interventions such as medication review have been implemented worldwide to reduce inappropriate prescribing for older adults. However, the implementability of such interventions are underexplored in the outpatient clinics in Singapore’s public hospitals. Hence, the Pro-M study aims to assess the feasibility of implementing a physician-pharmacist collaborative care intervention in geriatric medicine outpatient clinics to facilitate appropriate prescribing for older adults in Singapore.

**Methods:**

This is a single-arm, non-randomised feasibility study using a pre-post evaluation design. This study consists of two parts: (1) implementation phase of the intervention (6 months) and an (2) evaluation phase (3 months). Eligible patients will be recruited from geriatric medicine outpatient clinics at two public hospitals in Singapore through convenience sampling. The main components of the Pro-M intervention are: (1) pharmacist-facilitated medication reviews with feedback on any medication issues and potential recommendations to physicians, and (2) physicians communicating changes to other relevant prescribers. The evaluation phase will involve surveying and interviewing physicians and pharmacists involved in the implementation of the intervention. A mixed-method approach will be employed for data collection and analysis. The quantitative and qualitative findings will be triangulated and reported using Proctor’s implementation outcomes: appropriateness, penetration, acceptability, fidelity, feasibility, and sustainability. A basic cost analysis will be conducted alongside the study.

**Discussion:**

This is a phase 2 study to test the feasibility of implementing an intervention that was co-created with stakeholders during phase 1 development of an intervention to optimise prescribing for older adults with multimorbidity. The implementation will be assessed using Proctor’s implementation outcomes to provide insights on the process and the feasibility of implementing medication reviews for older adults with multimorbidity as a routine practice in outpatient clinics. Data collected from this study will inform a subsequent scale-up study.

**Trial registration:**

ClinicalTrials.gov Identifier: NCT05756478. Registered on 06 March 2023.

**Supplementary Information:**

The online version contains supplementary material available at 10.1186/s13690-024-01264-x.

**Table Taba:** 

**Text box 1. Contributions to the literature**
• The Pro-M study aims to assess the feasibility of implementing medication review for older adults with multimorbidity in a busy clinical setting such as the geriatric medicine outpatient clinics in Singapore.
• This study would observe the direction of the effects of a physician-pharmacist collaborative care intervention in reducing potentially inappropriate medications in older adults attending hospital-based geriatric medicine clinics.
• The results will inform future plans to scale up the Pro-M intervention in other outpatient specialists’ clinics in Singapore.

## Introduction

An ageing population is a rising concern around the world. In 2022, 18.4% of Singapore’s population were aged 65 and above, and this number is predicted to increase to 23.8% in 2030 [1]. Among older adults, multimorbidity of having at least two or more chronic conditions is a common occurrence [2, 3] and in Singapore, one study identified 51.5% of older adults aged 60 and above to have multimorbidity [4]. Multimorbidity is often associated with polypharmacy, which is often defined in literature as taking five or more medications concurrently [5]. Polypharmacy increases one’s risk of experiencing negative clinical outcomes, such as adverse drug reactions (ADRs), falls, and hospitalization [6]. It also increases the likelihood of potentially inappropriate prescribing (PIP) [7]. One of the reasons for the increased risk is that most clinical guidelines and evidence for disease management are focused on treating a single disease [8]. However, polypharmacy can be considered appropriate when the medications prescribed are in line with best evidence [8]. Therefore, being prescribed appropriate medications is more critical, regardless of the numbers [9]. Nonetheless, prescribing for older adults with multimorbidity can be a complex task with the need to factor in various diagnoses as well as the decline in their physiological conditions [10, 11].

Interventions to address PIP among older adults have been conducted worldwide, spanning from pharmacist-related interventions, education, and the involvement of a multidisciplinary team [12–14]. Prescribing tools such as Beers criteria [15], Screening Tool of Older People’s Prescriptions (STOPP) criteria, and Screening Tool to Alert to Right Treatment (START) criteria [16] have also been used to assess inappropriate medication use in older adults [13]. A scoping review has identified medication review as an element in almost 70% of the interventions aimed at reducing PIP among older adults, with an average of 2.5 elements per intervention [17]. Additionally, a review by Bloomfield et al. (2020) assessed the effectiveness of deprescribing interventions for community-dwelling older adults and found that comprehensive medication review may have reduced potentially inappropriate medications (PIMs), along with a slight reduction in mortality [18].

In a Singapore study conducted in 2019, the prevalence of polypharmacy in community-dwelling older adults in Singapore was found to be around 14.5% and is correlated with medication non-adherence [19]. Other factors, such as age (85 years and above), gender (male), health conditions, and ethnicity (Malay or Indian) also increase one’s likelihood of having polypharmacy [19]. Similarly, 58.6% of nursing home residents were exposed to polypharmacy, with PIP observed in 70% of the residents [20]. There have also been efforts to optimise prescribing for older adults in Singapore. A local study done in the nursing homes setting found pharmacist medication reviews beneficial and improve the quality of life and care for the residents indirectly [21]. Another study conducted in the inpatient setting using an implicit tool, recommended its use to review and identify inappropriate medications in a busy setting [22]. However, medication reviews are not part of routine practice in the busy outpatient clinics, due to the time and coordination needed. Hence, the feasibility and effectiveness of implementing such an intervention in the outpatient setting is unknown.

Since medication review in settings like the outpatient clinics has not been well-studied, we embarked on a phase 1 intervention-development study, using theory- and evidence-based, implementation-based, and partnerships approaches to co-create an intervention with relevant stakeholders to address potential contextual challenges. Details on the intervention development process was published in a separate paper [23].

The resulting intervention, Pro-M or Appropriate Prescribing for older adults with Multimorbidity, is a physician-pharmacist collaborative care intervention to optimise prescribing for older adults with multimorbidity at outpatient specialist clinics in Singapore’s public hospitals. The main component is a pharmacist-facilitated medication review, with physicians communicating changes to other relevant prescribers. This second phase study aims to evaluate the feasibility of the intervention from the perspectives of the physicians and pharmacists involved in the implementation. The rationale of conducting a feasibility study is to test and evaluate the implementation of the intervention in real-world settings and identify potential implementation challenges that need to be addressed and adapted for the full-scale study in order to reduce potential resource wastage [24, 25]. As the intervention was co-created with stakeholders from the two study sites, our conjecture is that the implementation of the intervention would likely be feasible to the physicians and pharmacist. In addition, our study aims to provide quality care to the older population in Singapore, which aligns with the Singapore’s Voluntary National Review [26] which takes guidance from United Nations’ Sustainable Development Goals (SDGs) [27] on the goal of good health and well-being.

### Study aims and objectives

The aims of the study are:

To assess feasibility of the intervention among stakeholders using Proctor’s implementation outcomes [28]: Appropriateness, Penetration, Acceptability, Fidelity, Feasibility, and Sustainability (primary).To collect data on recruitment rate for sample size calculation in the next phase scale-up study (secondary).To collect pre-post data on the prevalence of PIMs and/or other medication issues for sample size calculation in the next phase scale-up study (secondary).To conduct a cost analysis of the intervention based on manpower cost and the cost of PIMs and/or medications with other issues identified before and after the medication reviews (secondary).

## Methods

### Study design

This is a single-arm, non-randomised feasibility study using a pre-post evaluation design. Any medication changes related to PIM and other medication issues before and after medication review will be compared. An explanatory sequential mixed method approach will be used for data collection and analysis, where the qualitative findings (e.g., interviews) will be used to explain the quantitative findings (e.g., recruitment rate, implementer survey results) [29]. This study consists of two parts: (1) implementation phase of the intervention (6 months) and an (2) evaluation phase (3 months). An outline of the feasibility study including the intervention and evaluation phases is shown in Fig. 1. Ethics approval was obtained from National Healthcare Group Domain Specific Review Board (NHG DSRB) domain F (Ref. no: 2022/00491). The reporting of this protocol is guided by the standard protocol items: recommendations for interventional trials (SPIRIT) [30] (see Additional file 1: SPIRIT 2013 checklist). The Clinical Trial registration for this study is NCT05756478.

**Fig. 1 Fig1:**
[figure not shown]
Overview of the Pro-M study design

### Setting

The study will be conducted at the geriatric medicine (GRM) outpatient clinic of two public acute hospitals in Singapore. In Singapore, 80% of the primary care is provided by the private sector but the opposite is observed for secondary care (e.g., outpatient settings) [31, 32]. As our study target older adults, GRM outpatient clinics providing care to older patients with multiple chronic conditions are the ideal location to trial the intervention. Furthermore, the intervention was co-created with the stakeholders from both study sites and that medication review for older adults with multimorbidity is not a routine practice. The clinic physicians are invited to refer eligible patients to the study, while the pharmacists conducting medication reviews are part of the study teams at each hospital site.

### Screening and recruitment of patients

Eligible patients will be pre-screened and invited to join the study by their attending GRM physicians through convenience sampling. The inclusion criteria are as follow: aged 65 and above, current patient of GRM outpatient clinic, and taking five or more medications daily. On the other hand, patients will be excluded if they are below 65 years old, currently receiving other types of pharmacist services (e.g., medication therapy management), are unable to understand and communicate in English, Chinese, or Malay and if patient or caregiver decline to participate in the study. Participation in this study is fully voluntary, and if they agree to participate, written informed consent will be taken face-to-face by a study team member at each hospital. There is no consensus on the optimal sample size for pilot or feasibility studies and the size is dependent on the objective of the study [33]. Hence, we did not perform a sample size calculation. Instead, we consulted and discussed with stakeholders at both sites and agreed to recruit 30 patients per site for this study, which will provide sufficient insights into the implementation process.

### Intervention specification

The prototype for the intervention evolved from multiple scoping reviews and modified Delphi studies and was finalised through a co-creation exercise with stakeholders consisting of geriatricians and pharmacists at both study sites during phase 1. In summary, various theoretical frameworks and taxonomy, such as Theoretical Domains Framework (TDF), Behaviour Change Wheel (BCW), and Behaviour Change Techniques (BCTs), were employed at different time points to develop the intervention [34–36]. The detailed account of the intervention development process has been reported in another publication [23]. The main components for this intervention are: (1) pharmacist-facilitated medication review with feedback and recommendation to physicians and (2) physicians communicating medication changes made by other prescribers when needed. Table 1 shows the process of operationalisation of the BCTs in the Pro-M study.

**Table 1 Tab1:** Operationalisation of BCTs in Pro-M study

BCTs identified from modified Delphi study [37]	Context during phase 1 prototype development	Operationalizing BCTs in the Pro-M Study
Credible source	Pharmacists who are experienced in geriatric pharmacology	Medication reviews are led by pharmacists, who will be present at the clinic during review sessions
Restructuring the physical environment	Presence of pharmacist in clinics	
Instruction on how to perform the behaviour	Guidelines to assist in optimizing prescribing	Pharmacists will conduct medication review using prescribing tools (e.g., Beers Criteria)
Information about health consequences	Feedback from pharmacists on occurrence of PIMs post-medication review	Physicians will receive patient-specific feedback on PIMs or other medication issues identified by pharmacists
Feedback on outcomes of behaviour		
Problem solving	Physicians will identify medication problems and/or discrepancies, and then discussing with pharmacists as well as patients for necessary changes to be made	Physicians will ascertain medication review outcomes and any recommendations from the pharmacists, before making the next prescribing decision (e.g., to reduce PIMs)
Goal setting (outcome)		
Goal setting (outcome)	Ensuring proper documentation on reasons behind addition or removal of medications and provide feedback to other relevant prescribers	Documentation of medication indications and communicating changes to other relevant prescribers
Feedback on outcomes of behaviour		

As our intervention was developed with the considerations on integrating medication review into routine outpatient care, variations in the delivery format between the sites were accommodated, due to the operational context and preference in practice at each site. For instance, there are two modes of recruiting eligible patients at both sites. One site has the option of calling patients beforehand to introduce the study, whereas the other site will mainly recruit patients on-the-spot during the day of appointment. Patients who consent to participate in the study will undergo a one-time medication review with a pharmacist. Medication review will be conducted either in-person or through a tele-med consultation, using preferred prescribing tools of choice (e.g., Beers criteria, STOPP/START) by the site pharmacists. Findings of any PIMs and other issues will be highlighted to the physicians so that they could take this information into consideration when making prescribing decisions during their consultations with patients. The changes would then be documented and communicated to the patients and other relevant prescribers via discussions or a memo. The feasibility of implementing medication reviews in routine outpatient practice among the stakeholders (patients, physicians, pharmacists) will be evaluated through surveys. In addition, in-depth interviews will also be conducted with selected implementers (physicians and pharmacists) to understand additional barriers experienced in the implementation process.

### Outcome measures

#### Primary outcome and data collection

The primary focus of this study is to assess the feasibility of implementing the physician-pharmacist collaborative care intervention from the stakeholders’ perspectives, which will be reported qualitatively. Surveys will be conducted to explore stakeholders’ attitudes and experiences during the intervention. In-depth interviews will follow with selected implementers to elicit insights as well as qualitative interpretations to the survey findings.

A short 11-item patient survey (see Additional file 2: Pro-M patient survey) will be administered after the intervention to measure patients’ attitudes toward acceptance and appropriateness of the intervention. They will also be asked if they will be willing to pay for medication review as part of their routine care in the future. On the other hand, physicians and pharmacists involved in the intervention will be invited to participate in the evaluation phase. To achieve this goal, a 25-item implementer survey was developed using Proctor’s implementation framework (Penetration, Appropriateness, Acceptability, Fidelity, Feasibility, and Sustainability) [28] and each item will be measured using a 5-point Likert scale (see Additional file 3: Pro-M implementer survey).

In addition, some quantitative data, such as time taken to conduct the medication review, number of discussions between physicians and pharmacists, number of communication efforts by the physicians, and the number of agreements between the physicians and the pharmacists on PIM and other medication issues identified, will be collected alongside the intervention. This quantitative information will be triangulated with the survey and interview results to provide a fuller picture on the feasibility of the intervention.

#### Secondary outcomes and data collection

To provide information for sample size calculation for the next phase scale-up study, the average number of PIMs per patient before and after medication review and the prevalence of PIMs among patients will be collected. For the purpose of this study, prevalence is defined as having at least one PIM prescribed. Medication data on identified PIM and other medication issues will be collected over two time points: once during the medication review and a retrospective data collection from patient’s last GRM appointment. The retrospective data will form the comparison and represent ‘usual care’ where medication review is only done in an ad-hoc and informal basis, if any. This comparison will help to ascertain if medication reviews impact physicians’ prescribing decisions in any way.

In addition, a basic cost analysis will be conducted to compare the cost of manpower for medication review and the cost of PIMs or other medications issues identified before and after the medication reviews. Manpower cost to conduct medication reviews will be estimated by the time needed to a conduct a medication review. Cost of PIMs and other medication issues identified and resolved will be collected to estimate the monthly cost savings from discontinued medications and any substituted medications, if there are [21]. The unit cost of medications will be calculated using the private costs of medications before government subsidies. The cost information collected will provide insights on the longer-term sustainability of implementing medication review in routine care for older adults with multimorbidity.

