### Data analysis

#### Quantitative data

Descriptive statistics will be used to report patients’ characteristics, the prevalence of PIMs and other medication issues identified, and results from the patient and implementer surveys. We plan to observe the direction of impact of medication review on PIMs and other medication issues identified. In addition, a paired t-test for the difference in two means will be used to determine any changes in PIMs before and after medication reviews, which could be used to estimate the effect size for sample size calculation during the next phase scale-up study.

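### The before-after comparison of PIMs and other medication issues does not fix the same ascertainment at both points, and its later count precedes the prescribing decision

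*Protocol article*

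**What the plan says.** The protocol article, Secondary outcomes and data collection, states what is wanted: "the average number of PIMs per patient before and after medication review and the prevalence of PIMs among patients will be collected". It then names two collection points for PIMs and other issues: "collected over two time points: once during the medication review and a retrospective data collection", the second relating to the patient's previous geriatric medicine visit. The retrospective data are the comparator and stand for usual care, "where medication review is only done in an ad-hoc and informal basis, if any". The purpose is given as an inference about prescribing: "This comparison will help to ascertain if medication reviews impact" what physicians decide to prescribe.

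Intervention specification describes the live point. On its format it says: "Medication review will be conducted either in-person or through a tele-med consultation". The choice of criteria is left to each site, "using preferred prescribing tools of choice (e.g., Beers criteria, STOPP/START) by the site pharmacists". The results go to the physician ahead of the prescribing decision: "Findings of any PIMs and other issues will be highlighted to the physicians so that they could take this information into consideration".

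Quantitative data, under Data analysis, gives the reading: "We plan to observe the direction of impact of medication review on PIMs and other medication issues identified". It plans a paired t-test on PIMs and says the result could supply an effect size for the scale-up study. The study has one arm and aims for 30 patients at each of two sites. No sample size calculation was done.

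**The concern.** What is compared is the number of issues identified, and the intervention is itself a way of identifying issues. Better detection at the review pushes the later count up; better prescribing pushes it down. Unless ascertainment is the same at both points, the sign of the difference cannot be read as the direction of effect on prescribing, which is what the study says it will observe.

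The order of events adds a second problem. A count taken during the review comes before the physician has acted on it, so it cannot yet contain any prescribing change that the review causes.

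Three uses depend on this comparison: the direction of effect, the possible effect size for the scale-up sample size, and the cost analysis, which also draws on issues found before and after the review. The limitations in the Discussion cover convenience sampling, small numbers and language, but not this. Small numbers add random error; unequal ascertainment adds bias, which a larger sample does not remove.

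**Working it through.** **Plan's own figure.** There is none to reproduce. The article gives no effect size, SD, alpha or power for this comparison. The only arithmetic is 30 × 2 = 60 patients.

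**The two points side by side.**

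| | Earlier point | Later point |
|---|---|---|
| Source | Retrospective, previous clinic visit | Live pharmacist consultation |
| Patient contact for the count | None stated | Yes, in person or by tele-med |
| Who identifies issues | Not stated | Site pharmacist |
| Criteria | Not stated | Tool chosen by the site pharmacist |
| Relative to the physician's post-review decision | Before | Before |

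Nothing links the criteria, assessor or source in one column to those in the other. In the last row both counts precede the decision. Read literally, their difference can contain a detection difference and any drift since the earlier visit, but not the prescribing response to the review.

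**Direction of the bias, supposing the later count did follow the decision.** Let *m* be the true mean number of PIMs per patient at the earlier point, *r* the true proportional reduction, and *s_E* and *s_L* the shares captured at the earlier and later points.

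Expected observed change = *m* [(1 − *r*) *s_L* − *s_E*].

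This is zero when *s_E*/*s_L* = 1 − *r*, and has the wrong sign when the ratio is lower. The condition does not involve *m* or the SD. If *s_E* = *s_L*, the sign and the proportional reduction are preserved.

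Taking *s_L* = 1 and *m* from 1.0 to 2.0 (all assumed):

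| True reduction | *s_E* | Expected observed change per patient |
|---|---|---|
| 0 | 0.9 | +0.10 to +0.20 |
| 0 | 0.6 | +0.40 to +0.80 |
| 30% | 1.0 | −0.30 to −0.60 |
| 30% | 0.8 | −0.10 to −0.20 |
| 30% | 0.7 | 0 |
| 30% | 0.6 | +0.10 to +0.20 |

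**Effect on the paired t-test.** This depends heavily on the assumed SD of the change, so two versions are shown for *m* = 1.5, *s_L* = 1 and no true change.

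- SD of change 1.0: SE = 1.0/√60 = 0.129. Earlier capture of 90%, 85% or 75% gives 1.5 × 0.10 = 0.15, 1.5 × 0.15 = 0.225 or 1.5 × 0.25 = 0.375, hence t = 1.16, 1.74 or 2.90. Only the last is significant at the two-sided 5% level.
- Poisson counts in which the change consists only of missed PIMs: at 90% capture the variance is 1.5 × 0.10 = 0.15, the SD 0.387 and the SE 0.387/√60 = 0.050, so t is about 0.15/0.050 = 3.0. In 4000 simulated studies of 60 pairs, 96% showed a significant increase (81% with *m* = 1.0).

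With a true 30% reduction and *m* = 1.5 in the same simulation, a significant decrease appeared in 100% of studies at equal capture, 93% at 90% earlier capture, 33% at 80% and 2.5% at 70%. At 60%, 28% showed a significant increase.

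The two versions disagree at the same 90% capture rate (t of 1.16 against about 3.0). No particular chance of a false result can therefore be claimed. What holds whatever the SD is the cancellation condition above.

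**The case against.** The strongest reply is that unequal detection of PIMs is inferred, not stated. The article does not say who screens the earlier record or how. The remark about ad hoc, informal review describes the care patients had received, not the study's method of extraction. A study pharmacist applying the same explicit criteria to the earlier list would fit the text equally well, and prescribed PIMs can largely be screened from a list. The planned t-test concerns PIMs only, so the concern is strongest for other issues, where no test is planned. The full protocol may give the extraction procedure, and a condensed article may leave it out. Finally, the outcome is secondary, and the article disclaims effectiveness as an aim and adequate power.

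Much of this stands. A reader might infer that the two PIM counts certainly come from different detection methods; the text supports only that common ascertainment is not fixed. A reader might also infer that other medication issues have no valid earlier value at all. The article does not define them, and some could be visible in a record, so that goes too far.

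What does not stand is the appeal to brevity. The article itself names the two sources, makes the retrospective one the comparator, and draws the inference about prescribing. For issues that need a conversation with the patient, those sources are unlike as written. The order of review and prescribing decision is also stated in the article and does not fit a comparison of before with after.

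**Conclusion.** The point holds as a moderate one. As written, the comparison does not separate a change in detection from a change in prescribing. For issues that surface only through patient contact this follows from the stated sources. For PIMs it is possible and not excluded; its size is unknown, and it would be small if the same explicit criteria were applied to the earlier list.

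Separately, a count made during the review is not a post-review prescribing count, so the two stated time points and the before-and-after wording need to be reconciled. A reader might infer that the study will hold no post-decision information at all. That is not supported: Study design speaks of comparing medication changes before and after review, and the cost analysis collects issues that were resolved. The gap is that neither of the two time points named for the PIM count is defined as falling after the decision.

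All magnitudes are illustrative, since the mean, SD and capture rates are assumed. The consequence is confined to a secondary outcome, but one of its stated uses is planning the scale-up study.

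**What to change.** - For the PIM comparison and the paired t-test, have the same assessor apply one fixed set of criteria to two recorded medication lists: the list from the previous geriatric clinic visit and the list recorded after the physician's post-review decision. State this second time point explicitly and reword Secondary outcomes and data collection and Quantitative data to match. This concerns outcome assessment only; the pharmacists' choice of tool for the review itself need not change.
- Take issues found only through patient contact out of the pre-post comparison. Report them as the yield of the review: number found, number agreed between physician and pharmacist, number resolved. The article already plans to collect most of these counts under its primary and secondary outcomes.
- If the full protocol already prescribes common screening, one sentence saying so would settle the PIM part; the time point would still need defining.

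The cost is some rewording and a second screening of recorded lists for about 60 patients. The downside is that medicines absent from the clinic record are missed at both points. The change removes the detection component only; with no control arm, changes since the earlier visit that have other causes remain in the difference.

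### As written, neither PIM time point falls after the physician's decision, so the secondary pre-post PIM comparison does not capture what the review led physicians to change

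*Protocol article*

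**What the plan says.** Under Secondary outcomes and data collection, the article names the outcome as the mean number of PIMs per patient before and after the review, together with the proportion of patients with at least one PIM. It then fixes when the data are taken: "collected over two time points: once during the medication review and a retrospective data collection" from the last geriatric medicine appointment. The retrospective point is the comparator and stands for usual care. The purpose is explicit: "This comparison will help to ascertain if medication reviews impact physicians’ prescribing decisions in any way".

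Under Intervention specification, each patient has one review, in person or by tele-consultation. Its findings are "highlighted to the physicians so that they could take this information into consideration when making prescribing decisions" in the consultation, and changes are documented and communicated after that.

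Study design states: "Any medication changes related to PIM and other medication issues before and after medication review will be compared". The analysis section adds that "a paired t-test for the difference in two means will be used to determine any changes in PIMs before and after medication reviews", and that the result could supply the effect size for the scale-up sample size.

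**The concern.** A before-and-after comparison needs one measurement on each side of the action it evaluates. Here the action that can change a patient's PIM count is the physician's decision, informed by the review. The last appointment is clearly before it. A count taken during the review also comes before it, because the decision waits for the review's findings. The article therefore gives two time points that do not supply the after value its own outcome and purpose require.

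At stake are the direction of effect on PIMs that the study hopes to observe, and the effect size that may be carried into planning the next study. Collecting pre-post PIM data for that sample size is one of the listed secondary aims.

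**Working it through.** **Order of events, from the article**

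1. Last geriatric medicine appointment: PIM data collected retrospectively (Secondary outcomes and data collection).
2. Interval between visits, in which any prescriber may change the list.
3. Medication review by the pharmacist: PIM data collected (same section).
4. Findings passed to the physician, who decides in the consultation (Intervention specification).
5. Changes documented and communicated (Intervention specification).

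PIM counts are assigned to steps 1 and 3. None is assigned to step 4 or later.

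**What each contrast contains**

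Let L be the mean PIM count on the list leaving the last appointment, E on the list entering the review visit, and P on the list after the physician's decision. Let a be any difference in ascertainment between the in-review count and the retrospective count.

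- As written: D = (E − L) + a. P does not appear, so D is the same however many PIMs the physician resolves.
- Change at the reviewed visit: P − E.
- Change since the last appointment: P − L = (P − E) + (E − L). This contains the physician's response but also whatever changed between visits.

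**Illustration with assumed inputs (none is in the article)**

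Assume 60 patients (30 per site × 2 sites, the only figure here from the article), a mean of 1.5 PIMs, and equal ascertainment (a = 0). Assume also that 5% of PIMs are lost and 0.075 gained per patient between visits. Net drift is then −0.05 × 1.5 + 0.075 = 0. If physicians resolve a fraction r after the review, P − E = −r × 1.5.

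| r (assumed) | D as written (simulated) | P − E by formula | P − E simulated |
|---|---|---|---|
| 0% | 0.00 | 0 | 0.00 |
| 25% | 0.00 | −0.375 | −0.38 |
| 50% | 0.00 | −0.75 | −0.75 |
| 75% | 0.00 | −1.125 | −1.13 |

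The table shows only that D does not respond to r. It does not estimate what the study will see.

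**Does the sample size help?** With n = 60 the 95% confidence interval for a paired mean difference has half-width t(0.975, 59)/√60 ≈ 0.26 SD of the differences. That describes precision around D. It does not make D the intended quantity.

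The article states no power calculation or expected effect, so there is no figure of its own to reproduce.

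**The case against.** The best defence is that the reference to the review is loose wording for the whole review visit, including its outcome. The same section speaks of before and after, Study design speaks of medication changes, the Discussion expects to record any reduction in PIMs, and changes are documented as part of the intervention. The article is also a condensed account, and the exact moment of extraction might sit in a fuller protocol. This has weight as to intent. But the article is not silent: it fixes the number and timing of the measurements, and as fixed they conflict with its own outcome and purpose. If the whole visit was meant, the wording still needs correcting, and the contrast becomes P − L, which mixes in between-visit changes.

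Three stronger readings are tempting and should not be drawn.

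- *The study cannot show whether prescribing changed.* It collects physician-pharmacist agreements, documented changes, and issues identified and resolved with savings from discontinued or substituted drugs. These reflect the physician's response. They are just not designated as the after value of the paired comparison.
- *Closer detection at the review will make PIMs appear to rise.* The article does not say who scores the retrospective data or with what tool, so a difference in ascertainment is possible but not shown. A reversed sign would rest on assumption alone.
- *Using the last appointment as both baseline and usual-care comparator is a contradiction.* It is inherent in a declared single-arm pre-post design.

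It is also fair to say that P − E alone is no clean answer. It credits the review with changes the physician would have made anyway, and E − L contains no geriatric consultation that could correct for this.

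**Conclusion.** The point holds as an error in the stated time points, confined to the secondary pre-post PIM comparison. Followed literally, the paired test and the effect size drawn from it measure between-visit drift plus any ascertainment difference, and exclude the prescribing decision they are meant to reflect. This rests on reading the review and the consultation as separate, ordered steps, as Intervention specification describes them.

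No numeric magnitude follows from the document. The limitations section says effectiveness is not an aim and power is inadequate. That lowers the stakes for this study, but does not make the contrast suitable for planning the next one.

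**What to change.** 1. Define the after count as the PIMs on the medication list once the physician's decision at the review consultation is recorded.
2. Score three lists per patient with the same tool and in the same way: leaving the last geriatric medicine appointment (L), entering the review visit (E), and after the decision (P).
3. Report both P − E and P − L. Label P − E as change at the reviewed visit, which may include changes the physician would have made anyway. Label P − L as the article's usual-care comparison, which includes between-visit changes.
4. State in advance which of the two feeds the scale-up effect size.
5. Reconcile the wording in Study design, Secondary outcomes and data collection, and the quantitative analysis section.

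The cost is these wording changes and about one extra list extraction per patient, roughly 60 in all at 30 per site. Changes made at the consultation are already to be documented, so the source material should exist. This is a change to measurement and reporting only and does not touch patient care.
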